#### 8.1.1 SCR – Screening (week -1)

SCR visit will take place in the HIV units of both HGTP and HC.

Site personnel will obtain informed consent. After patient acceptance, inclusion and exclusion criteria will be reviewed and following procedures will be performed:

- Data collection: demographics, baseline HIV drug resistance genotype information, last hepatitis C and B, and syphilis serology, last laboratory tests, history of cART regimens, history of past and foreseen vaccinations.
- cART adherence assessment (SERAD questionnaire)
- Blood extraction (if no lab tests available within 3 months or Hepatitis B/C or syphilis RPR within 6 months prior to screening visit), including pregnancy test.
- Plasma and PBMC storage following scheme detailed in attachment K
- Provide a calendar with all the planned visits.
- MVA1 and MVA1+1w visits scheduling

#### 8.1.2 MVA1 – First MVA vaccination (week 0)

Before MVA1 visit, study physician will review all inclusion and exclusion criteria and if all vaccination criteria are met, will prescribe the vaccination using the **MVA.HIVconsv prescription form** (attachment L).

MVA1 visit will take place in UPIC (HGTP) and by FLS study nurse and FLS physician.

In MVA1 visit, procedures to be performed will be:

- Measurement of vital constants (blood pressure, temperature and cardiac rate)
- cART adherence assessment (SERAD questionnaire)
- Clinical visit including physical exam by the investigator physician pre and post vaccination
- Collection of MVA.HIVconsv vaccine from the Pharmacy Service

- Preparation of MVA.HIVconsv vaccine in the designated BL2 sterile hood located at IrsiCaixa following handling, thawing and preparation instructions detailed at the SOP (attachment I)
- Intramuscular administration of MVA.HIVconsv vaccine in both deltoid muscles
- Measurement of vital constants 10 and 30 minutes after MVA injection.
- Fill in the **MVA.HIVconsv administration form** (attachment C)
- Provide the patient with the **MVA diary card** (attachment F).
- Give instructions to fill diary card.

### 8.1.3 MVA1+1w – One week post- MVA1 vaccination (week 1)

The following procedures will be performed at both HIV units (HGTP and HC):

- Blood extraction including:
  - o Viral load, biochemistry (including Sodium, Potassium, Phosphate, Magnesium and Calcium) and hematological parameters.
  - o Plasma and PBMC storage following scheme detailed in attachment K
- cART adherence assessment (SERAD questionnaire)
- Revision of MVA diary card and record of adverse events in clinical records
- Clinical visit, adverse event register
- RMD1 visit explanation and scheduling
- CRF data collection

### 8.1.4 RMD1 – First romidepsin infusion (week 3)

RMD1 visit will take place in UPIC (HGTP). Patients will be admitted on the day before the administration (no later than 8pm).

During the evening before RMD administration, the following procedures will be performed by the UPIC study nurse:

- Take vital constants (blood pressure, temperature and cardiac rate)
- Blood extraction including:
  - o Biochemistry and hematological parameters via Hospital emergency laboratory.
- Pregnancy test
- Electrocardiogram (ECG)
- cART adherence assessment (SERAD questionnaire)

In the morning of RMD administration, the UPIC study physician will perform a clinical visit, review ECG and lab test results and will fill in the **romidepsin/ondansetron prescription form**. The study nurse will perform:

- Blood extraction including:
  - o Viral load, biochemistry (including Sodium, Potassium, Phosphate, Magnesium and Calcium) and hematological parameters and CD4 count.
  - o Plasma and PBMC storage following scheme detailed in attachment K (pre-RMD infusion, -4 hour time point of PK1)
- Review romidepsin and ondansetron prescription
- Administrate ondansetron iv.

- Collect romidepsin and ondansetron tablets from Pharmacy Service (already prepared by pharmacy personnel)
- Take vital constants (blood pressure, temperature and cardiac rate)
- Administrate romidepsin (4-hour infusion)
- Collect PK1 samples (see attachment K)
- Measurement of vital constants (blood pressure, temperature and cardiac rate) in the first 30 minutes after RMD infusion and within 30 minutes after RMD finalization
- Perform ECG within 30 minutes after RMD infusion, to be reviewed by study physician.
- Fill in **RMD1 administration form** (attachment B)
- Provide the patient with the **RMD diary card** (attachment G)
- Give instructions to fill in the diary card / fill in together while admitted.
- Give instructions to take ondansetron tablets. Provide patient with 6 ondansetron tablets. Take first ondansetron tablet while admitted.
- Both Study nurse and Study physician will monitor for appearance of clinical adverse events

In the morning of day after RMD administration, following procedures will be performed:

- Clinical visit by the investigator physician
- Measurement of vital constants (blood pressure, temperature and cardiac rate)
- Blood extraction including:
  - o Plasma and PBMC storage following scheme detailed in attachment K (post-RMD infusion, 20 hour time point of PK1).

#### 8.1.5 RMD1 + 3d – 3 days post RMD1 infusion (week 3+ 72h)

Following procedures will be performed at both HIV units (HGTIP and HC):

- Blood extraction including:
  - o Viral load, biochemistry (including Sodium, Potassium, Phosphate, Magnesium and Calcium) and hematological parameters and CD4 count
  - o Plasma and PBMC storage following scheme detailed in attachment K
- Revision of RMD diary card, lab tests and record of adverse events in clinical records
- Clinical visit, adverse event register
- RMD2 visit explanation and scheduling
- CRF data collection

#### 8.1.6 RMD2 – Second romidepsin infusion and MVA1+4w – Four weeks post MVA1 vaccination (week 4)

The day before of RMD2 visit, study physician will review lab test results from previous visit and will fill in the **romidepsin/ondansetron prescription form**.

RMD2 visit will take place in UPIC (HGTIP). Patient will be admitted in the morning of administration (7:30am). Following procedures will be performed:

- Blood extraction including:
  - o Viral load, biochemistry (including Sodium, Potassium, Phosphate, Magnesium and Calcium), hematological parameters and CD4 count
  - o Plasma and PBMC storage following scheme detailed in attachment K (pre-RMD infusion, -4 hour time point of PK2)
- Urine pregnancy test
- Revision of romidepsin and ondansetron prescription
- Administration of ondansetron ev.
- Collection of romidepsin and ondansetron tablets from Pharmacy Service (already prepared by pharmacy personnel)
- Measurement of vital constants (blood pressure, temperature and cardiac rate)
- Clinical visit by the investigator physician pre and post romidepsin infusion and revision of RMD diary card.
- Administration of romidepsin (4-hour infusion)
- Collection of PK2 samples (see attachment K)
- Measurement of vital constants (blood pressure, temperature and cardiac rate) in the first 30 minutes after RMD infusion and within 30 minutes after RMD finalization
- Perform ECG within 30 minutes after RMD infusion to be reviewed by study physician.
- Fill in **RMD2 administration form** (attachment B)
- Provide the patient with the **RMD diary card** (attachment G)
- Give instructions to fill in the diary card / fill in together while admitted.
- cART adherence assessment (SERAD questionnaire)
- Both Study nurse and Study physician will monitor for appearance of clinical adverse events
- Give instructions to take ondansetron tablets. Provide patient with 6 ondansetron tablets. Take first ondansetron tablet while admitted.
- RMD2 + 3d visit scheduling

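### RMD2 and RMD3 are prescribed on results 4 days old at infusion, and the visit text ties the panel drawn that morning to no check against the 7.3.2 limits

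*Protocol*

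**What the plan says.** Romidepsin is given at weeks 3, 4 and 5 (Protocol 6.3.1). Section 7.3.2 lists laboratory limits at which further romidepsin might be postponed, if the abnormality resolves within 7 days, or discontinued. It does not say which sample the limits apply to.

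**RMD2 and RMD3.** Under 8.1.6 the "study physician will review lab test results from previous visit and will fill in the" prescription form on the day before RMD2. Section 8.1.8 has the same wording for RMD3, timed only as before the visit. The previous visits are those at 72 hours (8.1.5 and 8.1.7), where the panel is "Viral load, biochemistry (including Sodium, Potassium, Phosphate, Magnesium and Calcium) and hematological parameters and CD4 count".

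On both infusion mornings a new panel is drawn: "Viral load, biochemistry (including Sodium, Potassium, Phosphate, Magnesium and Calcium), hematological parameters and CD4 count". The other steps before the infusion are a pregnancy test, "Revision of romidepsin and ondansetron prescription", ondansetron, "Collection of romidepsin and ondansetron tablets from Pharmacy Service (already prepared by pharmacy personnel"), vital signs, and "Clinical visit by the investigator physician pre and post romidepsin infusion and revision of RMD diary card".

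**RMD1.** Section 8.1.4 is different. On the evening before, the nurse draws "Biochemistry and hematological parameters via Hospital emergency laboratory". Next morning, "the UPIC study physician will perform a clinical visit, review ECG and lab test results and will fill in the" prescription form.

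**The concern.** The text names an older sample as the basis for prescribing and says nothing about using the newer one. A participant whose haemoglobin, neutrophils, lymphocytes, platelets, creatinine or transaminases cross a 7.3.2 limit between the 72-hour draw and the next infusion could be infused in full compliance with the visit text, although blood already taken that morning would show it.

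This matters because 6.3.1 calls romidepsin cytotoxic, 10.3 says information on adverse event rates at this dose is scarce, and grade 3 or higher events are part of the primary endpoint (5.3.1). RMD2 and RMD3 are also the infusions given after earlier exposure in the same course, which is when limits on further dosing have most to do.

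**Working it through.** The plan states no figure to reproduce. The check is a day count and a comparison of the visit texts.

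**Age of the results named for prescribing** (nominal schedule; infusions 7 days apart from 6.3.1, draw at 72 hours from 8.1.5 and 8.1.7). Take RMD1 as day 0.

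- RMD1+3d draw: day 3.
- RMD2 form, the day before infusion: day 6. Age = 6 - 3 = 3 days.
- RMD2 infusion: day 7. Age = 7 - 3 = 4 days.
- RMD3 infusion, from the RMD2+3d draw: 7 - 3 = 4 days. The age at prescribing cannot be fixed, because the day is not stated.
- RMD1, for comparison: drawn the evening before, so under 1 day.

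**What stands between the morning draw and the infusion**

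| Listed step (8.1.6, 8.1.8) | Names the morning results or 7.3.2? |
|---|---|
| Pregnancy test | No |
| Prescription revision | No; refers to the prescription only |
| Ondansetron | No |
| Collection of prepared drug | No |
| Vital signs | No |
| Physician visit | No; names the diary card only |

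No fast laboratory route is named for these mornings. The morning panel at RMD1 is not a gate either. The difference is that the panel supporting the RMD1 prescription is from the evening before.

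**Parameters needed for the check.** Section 7.3.2 limits haemoglobin, ANC, ALC and platelets (4) and creatinine, AST and ALT (3): 4 + 3 = 7. Viral load and CD4 count are not among these laboratory limits.

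**Reach.** With at most 24 participants (10.3), planned infusions are at most 3 x 24 = 72. RMD2 and RMD3 account for 2 x 24 = 48, or 48/72 = 67%. This is a ceiling on exposure, not a count of harms.

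**Effect of a wait on the day's timing.** Admission is at 7:30 (8.1.6, 8.1.8) and ondansetron precedes the infusion by 30 minutes (6.6.1), so the earliest possible start is 8:00. This ignores the time for the draw and the pregnancy test. A 4-hour infusion ends at 12:00 and the 8-hour PK sample falls at 20:00. The laboratory turnaround is not given; assuming 1 to 2 hours:

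- infusion start: 8:00 becomes 9:00-10:00;
- 8-hour PK sample: 20:00 becomes 21:00-22:00;
- 12-hour PD samples and end of observation: 20:00 becomes 21:00-22:00 if counted from infusion start, or 24:00 becomes 01:00-02:00 if counted from infusion end.

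**The case against.** The strongest reply has four parts.

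1. **A post-dose check already exists.** Each dose is followed at 72 hours by haematology, biochemistry and ions, a clinical visit and a review of the results, and the next prescription uses them. The documents give no standard by which a 4-day-old panel is inadequate. This stands. A reader might infer that RMD2 and RMD3 are given without laboratory review; that is wrong.
2. **Nothing is contradicted.** Section 7.3.2 names no sample, so it covers any available result, including that morning's. Its holds are discretionary, a physician sees the participant before infusion, and nothing forbids reading the results. This stands too. A reader might infer that the protocol breaches its own limits or tells staff to ignore current values. The text is only silent.
3. **The check may be in pages not shown.** The administration form (attachment B), the romidepsin SOP (attachment H) and the schedule of procedures (attachment J) are not in the public document. The point therefore concerns the visit text and cannot show that the check is missing from the plan.
4. **RMD1 has its own reason for a fresh panel.** The last scheduled panel before it is at week 1, about two weeks earlier, and it is the first exposure. This explains why the visits differ. It does not explain why blood drawn before RMD2 and RMD3 should go unused in the dosing decision.

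What survives is narrow: the visit text points the prescriber to an older sample when a newer one is in hand.

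**Conclusion.** The point holds for the visit text in 8.1.6 and 8.1.8. RMD2 and RMD3 are prescribed from a genuine post-dose panel that is 4 days old at infusion, and the haematology and biochemistry drawn that morning are tied to no check against 7.3.2. It should be changed, as a modest safety improvement.

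The figure of 48 infusions must not be read as 48 unsafe doses. The documents give no rate at which limits are crossed between day 3 and day 7, so the number of missed holds cannot be estimated and could be zero. No effect on an efficacy estimate is claimed.

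The conclusion assumes the nominal schedule and full enrolment of 24. If attachment B, H or J already requires the check, what remains is a mismatch between that attachment and the visit text.

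**What to change.** In 8.1.6 and 8.1.8:

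- Send the infusion-morning blood count (haemoglobin, ANC, ALC, platelets) and creatinine, AST and ALT through the hospital emergency laboratory already used at RMD1.
- Have the physician check these seven values against 7.3.2 at the prescription-revision step already listed, before the drug is prepared and infused.
- State that viral load and CD4 count need not be awaited.
- If attachment B, H or J already requires this, align the visit text with it.

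The limits and the 7-day postponement window stay as they are, and no extra visit or blood draw is needed.

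**Cost.** A short wait on two mornings, with the infusion and the PK/PD samples moved later by the same amount: 1 to 2 hours under the assumed turnaround, plus any preparation time that now follows the check. Preparing the drug only after the check avoids wasting a dose when an infusion is held. A hold can move that infusion by up to 7 days, and with it the reservoir sample one week after RMD3; 7.3.2 already allows for such holds.

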#### 8.1.7 RMD2 + 3d – 3 days post RMD2 infusion (week 4+72h)

Following procedures will be performed at both clinical sites (HGTIP and HC):

- Blood extraction including:
  - o Viral load, biochemistry (including Sodium, Potassium, Phosphate, Magnesium and Calcium) and hematological parameters and CD4 count
  - o Plasma and PBMC storage following scheme detailed in attachment K
- Revision of RMD diary card, lab tests and record of adverse events in clinical records
- Clinical visit, adverse event collection
- RMD3 visit explanation and scheduling
- CRF data collection

#### 8.1.8 RMD3 – Third romidepsin infusion (week 5)

Before RMD3 visit, study physician will review lab test results from previous visit and will fill in the **romidepsin/ondansetron prescription**.

RMD3 visit will take place in UPIC (HTIP). Patients will be admitted in the morning (07:30am). Following procedures will be performed:

- Blood extraction including:
  - o Viral load, biochemistry (including Sodium, Potassium, Phosphate, Magnesium and Calcium), hematological parameters and CD4 count
  - o Plasma and PBMC storage following scheme detailed in attachment K (pre-RMD infusion, -4 hour time point of PK3)
- Urine pregnancy test
- Revision of romidepsin and ondansetron prescription
- Administration of ondansetron ev.
- Collection of romidepsin and ondansetron tablets from Pharmacy Service (already prepared by pharmacy personnel)
- Measurement of vital constants (pressure, temperature and cardiac frequency)
- Clinical visit by the investigator physician pre and post romidepsin infusion and revision of RMD diary card.
- Administration of romidepsin (4-hour infusion)
- Collection of PK3 samples (attachment K)
- Measurement of vital constants (blood pressure, temperature and cardiac rate) in the first 30 minutes after RMD infusion and within 30 minutes after RMD finalization
- Perform ECG within 30 minutes after RMD infusion to be reviewed by study physician.
- Fill in **RMD3 administration form** (attachment B).
- Provide the patient with the **RMD diary card** (attachment G).
- Give instructions to fill in the diary card / fill in together while admitted.
- cART adherence assessment (SERAD questionnaire)
- Both Study nurse and Study physician will monitor for appearance of clinical adverse events
- Give instructions to take ondansetron tablets. Provide patient with 6 ondansetron tablets. Take first ondansetron tablet while admitted.
- RMD3 + 3d visit scheduling

#### 8.1.9 RMD3 + 3d – 3 days post RMD3 infusion (week 5 + 72h)

Following procedures will be performed at both HIV units (HGTIP and HC):

- Blood extraction including:
  - o Viral load, biochemistry (including Sodium, Potassium, Phosphate, Magnesium and Calcium) and hematological parameters and CD4 count
  - o Plasma and PBMC storage following scheme detailed in attachment K
- Revision of RMD diary card, , lab tests and record of adverse events in clinical records
- Clinical visit, adverse event collection
- RMD3 + 1w visit explanation and scheduling
- CRF data collection

#### 8.1.10 RMD3 + 1w – One week post RMD3 infusion (week 6)

Following procedures will be performed at both HIV units (HGTIP and HC):

- Blood extraction including:
  - o Viral load, biochemistry and hematological parameters and CD4 count

- Plasma and PBMC storage following scheme detailed in attachment K
- Revision of RMD diary card, lab tests and record of adverse events in clinical records
- cART adherence assessment (SERAD questionnaire)
- Clinical visit, adverse event collection
- MVA2 visit explanation and scheduling
- CRF data collection

#### **8.1.11 MVA2 – Second MVA vaccination and MVA1+9w – Nine weeks post MVA1 vaccination (week 9)**

Before MVA2 visit, study physician will review all vaccination criteria are met and will fill the **vaccination prescription form**.

MVA2 visit will take place in UPIC (HGTIP).

In MVA2 visit, as soon as patient arrives to UPIC, following procedures will be performed:

- Blood extraction including:
  - Plasma and PBMC storage following scheme detailed in attachment K
- Measurement of vital constants (blood pressure, temperature and cardiac rate)
- cART adherence assessment (SERAD questionnaire)
- Clinical visit including physical exam by the investigator physician pre and post vaccination
- Collection of MVA.HIVconsrv vaccine from the Pharmacy Service
- Preparation of MVA.HIVconsrv vaccine in the designated BL2 sterile hood located at IrsiCaixa following handling, thawing and preparation instructions detailed at the SOP (attachment I)
- Intramuscular administration of MVA.HIVconsrv vaccine in both deltoid muscles
- Measurement of vital constants 10 and 30 minutes after MVA injection.
- Fill in the **MVA.HIVconsrv administration form** (attachment C)
- Provide the patient with the **MVA diary card** (attachment F).
- Give instructions to fill in the diary card.
- MVA2+1w visit scheduling

#### **8.1.12 MVA2+1w – One week post- MVA2 vaccination (week 10)**

Following procedures will be performed at both HIV units (HGTIP and HC):

- Blood extraction including:
  - Viral load, biochemistry and hematological parameters.
  - Plasma and PBMC storage following scheme detailed in attachment K
- cART adherence assessment (SERAD questionnaire)
- Revision of MVA diary card and record of adverse events in clinical records
- Clinical visit, adverse event register
- MVA2 +4w visit explanation and scheduling
- CRF data collection

#### **8.1.13 MVA2+4w – Four weeks post- MVA2 vaccination (13 weeks)**

Following procedures will be performed at both clinical sites (HGTIP and HC):

- Blood extraction including:
  - Viral load, biochemistry and hematological parameters and CD4 count.

- Plasma and PBMC storage following scheme detailed in attachment K
- cART adherence assessment (SERAD questionnaire)
- Clinical visit, adverse event register
- MVA2 +8w visit explanation and scheduling
- CRF data collection

In cases where pVL is detected >20 copies/mL at MVA2 + 4w, an extra visit will be scheduled at MVA2 + 6w including the following procedures:

- Blood extraction including:
  - Viral load, biochemistry, hematological parameters and CD4 count.
  - Plasma and PBMC storage.
- cART adherence assessment (SERAD questionnaire)
- Clinical visit, adverse event register
- MVA2 +8w visit explanation and scheduling
- CRF data collection

#### **8.1.14 MAP – Monitored antiretroviral pause and MVA2+8w – Eight weeks post MVA2 vaccination (17 weeks)**

Following procedures will be performed at both clinical sites (HGTIP and HC):

- Blood extraction including:
  - Viral load, biochemistry and hematological parameters.
  - Plasma and PBMC storage following scheme detailed in attachment K
- cART adherence assessment (SERAD questionnaire)
- Clinical visit, adverse event register
- Review acceptability for cART interruption after interim analyses (which will be performed at week 13 and be provided by investigational team in advance and recorded in 'Indication for MAP phase' form, attachment X)
- Review acceptability for cART interruption regarding plasma viral load suppression (pVL below the limit of detection in 2 consecutive determinations, spaced at least 1 week, and recorded in 'Indication for MAP phase' form, attachment X)
- Phase 2 study explanation including: cART interruption, site, weekly clinical visit, qualitative plasma viral load monitoring, criteria for cART resumption.
- CRF data collection

Once analytical results are available, cART interruption will be confirmed telephonically by study physician and first visit in BCN-Checkpoint will be scheduled.

In cases where pVL is not undetectable for 2 consecutive determinations, MAP will be postponed and extra visits will be scheduled (every week if pVL is 20-500 copies/mL, every two weeks if pVL is >500 copies/mL) including the following procedures until acceptability criteria for cART interruption are met.

- Blood extraction including:
  - Viral load, biochemistry and hematological parameters.
  - Plasma and PBMC storage.
- cART adherence assessment (SERAD questionnaire)
- Clinical visit, adverse event register

## - CRF data collection

In cases where MAP is postponed after MVA2+12w, the ELISPOT immunomonitoring assay will be repeated to assess if the vaccine induced T cell responses has decreased significantly. The research team will consider both the immunogenicity analysis and dynamics of plasma viremia to indicate or discourage treatment cessation.

[figure not shown]

